**Trial registration number:**

Dutch Trial Registry (NTR), NL6140, protocol V.2.

Strengths and limitations of this studyThis study is a randomised controlled trial comparing a wearable-controlled mobile serious game for wrist rehabilitation with standard care, the first of its kind, to the authors’ knowledge.The study is sufficiently powered to show a clinically important difference in the outcome measurements of the primary endpoint.By measuring treatment adherence, both subjectively and objectively, a reliable comparison between patient-reported and objectively monitored treatment adherence can be made.The control group receives an accurate representation of the current standard of care.The analysing statistician will be blinded to randomisation group.

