### Interventions

After randomisation, patients start participation in the trial as soon as their fracture has been qualified as stable or consolidated, and patients are fit to start active exercises as determined by the clinician; this is either directly, or as soon as possible, but within 3–5 days after cast removal or successful operative fixation. Together with specialised hand and wrist physiotherapists and exercise therapists, a standardised protocol for the first 6 weeks—when most progress is to be expected—has been established that is both embedded within the game and explained to patients.^38^ All patients are instructed by their clinician to perform the hand and wrist rehabilitation exercises three to five times per day. In addition, patients receive a simple diary to complete, with instructions to register their frequency and duration of exercises daily, as well as any physical complaints they may have during exercising.

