**Figure 3 F3:**
[figure not shown]
Schematic timeline of the study showing the randomisation and follow-up planning, as well as the outcomes measured during each visit. ORIF, open reduction internal fixation; PRWE, Patient-Rated Wrist Evaluation; ROM, range of motion.

Patients in both study arms complete a questionnaire, that was specifically developed for this trial, on their self-efficacy, experiences and perceived effectiveness of their exercise programme. Pain scores on a Visual Analogue Scale are recorded, and patients are asked about the frequency, if any, of visits to a physiotherapist or occupational therapist. In addition, partial or complete return to work, or to normal functioning if patients were currently unemployed, is registered. Patients are reminded by the researcher to fill out their exercise diary at every follow-up visit and are asked to return their completed exercise diary at 6 weeks of follow-up. In the intervention group, the data on exercise frequency and duration, as well as ROM, will also be retrieved from the serious game. The frequency reported by patients in this group will be compared with the data from the game application, which stores all exercise data including frequency, duration and the ROM measured.

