### Data analysis

The primary outcome is the PRWE score at 6 weeks. This outcome is represented as the change in outcome scores from T0 to T2 (delta, T2–T0). An intention-to-treat analysis is performed, and any missing data are imputed. Data will be analysed using a two-sided t-test or the Mann-Whitney U test, depending on normality of the distribution.

For the secondary continuous outcomes (PRWE score at 2 and 12 weeks, ROM, grip strength, pain scores), a repeated measures analysis of variance will be performed, where group assignment (game group vs control group) is the between-subjects factor, and time of visit (baseline, 2, 6 or 12 weeks follow-up) is the within-subjects factor. In case of a non-normal distribution, generalised estimating equations will be used. An intention-to-treat analysis will be performed, and any missing data will be imputed using multiple imputation. Other (secondary) functional outcomes are analysed as a percentage of the unaffected wrist. Bonferroni correction is applied to all secondary outcomes to correct for multiple tests. Therefore, p values of <0.0045 will be considered statistically significant.

Baseline data and secondary outcomes include categorical data such as fracture type and treatment type. These data will be analysed using the Χ^2^ test, and outcomes will be presented as the differences in frequencies. P values of <0.05 are considered statistically significant. Treatment adherence is measured using a self-reported diary. The number of exercise sessions and the total duration of exercising are continuous variables that will undergo quantitative and qualitative synthesis using a two-sided t-test or a Mann-Whitney U test as appropriate.

The diaries that are handed in after the trial period are analysed for the percentage of days the diary is completed and the total estimated time of exercising. In the intervention group, these data are also compared with the total time of exercising as registered within the game. In addition, should not all diaries be completed, the number of diaries handed in after the study period is registered. These data are then analysed using the Χ^2^ test, and outcomes will be presented as the difference in frequencies.

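### Adherence is analysed as diary totals with no stated handling of blank days, and the diary is set against the game log without matching days, so blanks can hide over-reporting and unequal diary keeping can shift the comparison between arms

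*Protocol article*

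**What the plan says.** The Interventions section gives every patient, in both arms, a simple diary "with instructions to register their frequency and duration of exercises daily". The Data analysis section makes this diary the adherence instrument: "Treatment adherence is measured using a self-reported diary". It then names the variables to be tested between arms: "The number of exercise sessions and the total duration of exercising are continuous variables", compared by t-test or Mann-Whitney U test.

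Returned diaries are "analysed for the percentage of days the diary is completed and the total estimated time of exercising". The two quantities stand side by side. The total is not divided by, restricted to or adjusted for the days completed. The only stated response to incomplete diaries is to count how many are handed in and compare that count by a chi-square test.

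For the game arm, the Data analysis section adds that "these data are also compared with the total time of exercising as registered within the game". The Outcome measurements section says the same of frequency: "The frequency reported by patients in this group will be compared with the data from the game application". Neither sentence limits the comparison to days that have a diary entry. The strengths and limitations list says of this comparison that "a reliable comparison between patient-reported and objectively monitored treatment adherence can be made".

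**The concern.** A diary total taken over recorded days is exercise per recorded day multiplied by the number of days recorded. It therefore mixes two things: how much the patient exercised and how well the patient kept the diary. A blank day is a missing record, but a plain sum treats it as a day without exercise.

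Two results are at stake. The first is the check of self-report against the game log. The log is complete whether or not the diary was filled in, so blanks pull the diary total down while over-reporting pushes it up. A biased diary can then look accurate. This needs no imbalance between arms, only blank days. The second is the adherence comparison between arms, where unequal diary keeping would look like unequal exercise. Adherence is a named secondary outcome and the mechanism through which the Introduction expects the game to work.

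**Working it through.** The plan gives no figure for adherence or diary completion, so there is none to reproduce. All completion rates below are assumptions.

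**Inputs from the protocol article.** Diary window 6 weeks = 42 days; 3 to 5 sessions a day of 10 to 15 minutes (mid-values 4 and 12.5 used for illustration); 42 patients per arm from the sample size section.

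**Diary against game log.** Let c be the share of days completed, o the over-reporting on recorded days, and q the true exercise on a blank day relative to a recorded day. If the diary total is a plain sum:

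diary total / log total = c(1 + o) / [c + (1 − c)q]

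The ratio is 1, an apparently perfect match, when o = q(1 − c)/c. If blank days are like recorded days (q = 1), this is o = 1/c − 1:

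| Completion c | Over-reporting hidden |
|---|---|
| 90% | 11% |
| 80% | 25% (1.25 × 0.80 = 1.00) |
| 70% | 43% |
| 60% | 67% |

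If exercise on blank days is half that on recorded days (q = 0.5), 80% completion hides 0.5 × 0.2/0.8 = 12.5%. If no exercise was done on blank days (q = 0), nothing is hidden. The log can show which case applies, but only if play on blank days is looked at separately.

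**Between arms, expected totals.** With equal true exercise in both arms, 42 × 4 × 12.5 = 2,100 minutes, and q = 1:

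- 80% v 70% completion: 2,100 × 0.10 = 210 minutes apart, ratio 0.80/0.70 = 1.14.
- 90% v 70%: 2,100 × 0.20 = 420 minutes apart, ratio 1.29.
- 90% v 60%: 2,100 × 0.30 = 630 minutes apart, ratio 1.50.

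**Between arms, false-positive rate.** Simulation of total sessions, 20,000 trials, 42 per arm, equal true exercise (mean 4 sessions a day, SD 1 between patients), completion SD 20 points and independent of exercise. Both thresholds are shown because the Data analysis section sets 0.0045 for all secondary outcomes, while the paragraph that covers adherence states 0.05.

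| Completion | p<0.05 | p<0.0045 |
|---|---|---|
| 75% v 75% | 5.0% | 0.5% |
| 75% v 70% | 13.4% | 2.2% |
| 75% v 65% | 38.7% | 11.3% |
| 80% v 60% | 91.2% | 66.8% |

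The Mann-Whitney test gives much the same at 0.05 for the three unequal cases: 12%, 37% and 91%.

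A second simulation, of minutes (mean 50 a day, SD 20 between patients, completion SD 15 points, 4,000 trials, p<0.05), set raw totals beside minutes per completed day: 5% v 5% at 80/80 completion, 22% v 6% at 85/75, 71% v 5% at 85/65 and 95% v 5% at 90/60. The per-day measure keeps its level here because blank days were simulated to be like recorded days.

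**The case against.** A reader might infer that the plan counts blank days as no exercise. No sentence says so. The total is called an estimate, with no method given, and a derivation rule for partial diaries could stand in a full protocol or analysis plan that is not shown. This stands, and the silence alone would not be a finding. What remains is what the article does fix: totals as the adherence measures, and a comparison with the whole log total, while it foresees incomplete diaries. Day-matching is not excluded, but it is not what the text describes.

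Multiple imputation might be thought to cover blank days. That sentence belongs to the paragraph on PRWE, range of motion, grip strength and pain; adherence is not in its list.

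A reader might also infer that the game arm will keep better or worse diaries. The documents do not support either. Both arms get the same diary and the same researcher reminders at follow-up visits, and the game's push notification is a reminder to exercise, not to complete the diary. Automatic logging could reduce diary keeping, and daily prompts could raise it. The 91% false-positive rate needs an assumed 20-point gap; at the 0.0045 threshold, gaps of 10 and 5 points give 11% and 2%.

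The percentage of days completed is already to be analysed, so unequal diary keeping would be visible. That is a real safeguard, but it does not correct the total that is tested or separate blanks from over-reporting in the log comparison. Finally, exercise per completed day is not free of bias: if patients leave days blank because they did not exercise, it overstates adherence. This stands, and it is why that measure should accompany the total and not replace it.

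**Conclusion.** The point holds conditionally. The article analyses diary totals while expecting partly completed diaries, and compares diary with game log without matching days. If the total is a plain sum, blanks hide over-reporting of 1/c − 1 per recorded day in the log comparison: 11% at 90% completion and 25% at 80%, assuming exercise on blank days matches that on recorded days, and less if patients exercised less on those days. This is the firmer part, because it needs no difference between arms and bears on a comparison that the article presents as reliable.

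The effect on the between-arm comparison depends on a completion gap whose direction and size are unknown. It is a risk to guard against, not a predicted false result. The matter concerns a secondary outcome only.

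**What to change.** - **Log comparison (game arm).** Compare diary and game log, for sessions and for minutes, only on days that have a diary entry. Report logged play on blank days separately; this shows in the game arm whether a blank means no exercise.
- **Between-arm comparison.** State that the planned totals count blank days as zero, and show sessions and minutes per completed diary day beside them. Read both with the already planned percentage of days completed, and claim a difference in adherence only if the two measures agree.

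The cost is a change of wording and a little more analysis. No new data are needed: the diary is daily and the app stores all exercise data. The downside is that the per-day measure overstates adherence where days are left blank because no exercise was done. The log can inform that question only for the game arm, so carrying the answer over to the control arm remains an assumption. The primary PRWE analysis and the sample size do not change.

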### Patient and public involvement

Patients were involved during development, playtesting and previous validation of the game. No patients were involved in the design, recruitment or conduct of this study. Results of the study will be published on the trial website, which is available publicly. The burden of the intervention has been evaluated by patients taking part in a specialised rehabilitation programme at a hand and wrist physiotherapy practice. They considered playing the game to be a comparable burden with their prescribed exercises.

## Ethics and dissemination

This study will be conducted according to the principles of the Declaration of Helsinki (64th World Medical Association (WMA) General Assembly, Fortaleza, Brazil, October 2013) and in accordance with the Medical Research Involving Human Subjects Act (WMO). The dataset will be made available and results of our study will be published unreservedly through academic journals, (international) conferences and popular media.

The medical risks of this trial are considered to be low, since treatment of both the intervention and the control group complies with national guidelines for standard treatment of distal radius fractures. Participation, or the choice to not participate, will not have any effect on any part of patient treatment or on the quality of medical care for patients.

Storing and processing of all patient data occurs in compliance with the General Data Protection Act, and a data processing agreement has been established between the app manufacturer and the hospital leading the trial. Digital data gathered by the individual mobile applications have been assessed using a Data Privacy Impact Assessment, and approved of by the hospitals’ data privacy officer. All digital data are stored on a computer server located within the highly secured hospital network and can only be accessed by the researchers after logging in with their personal account. The compliance with these rules ensures that privacy risks are minimised.

All data regarding the trial subjects are stored in a secure location in a locked cabinet that can only be accessed by study personnel. Data are anonymised and stored according to subject number. A linking log is stored separately from the data. All data, both digital and hardcopy, are stored for 15 years after trial completion according to WMO regulations.

## Discussion

There is a rapid increase in the use of technological applications for healthcare support and patient self-management.^33 42 43^ Clinical research on the effectiveness of these innovative applications is still scarce, however.^32^ ‘Wearables’ show potential as monitoring devices, since they are non-obtrusive and can monitor patients over longer periods of time.^44^ In addition, serious games have shown their own potential in education, improving both motivation and learning outcomes,^45 46^ and have also shown to be promising tools to increase self-efficacy; an important factor contributing to treatment adherence and physiotherapy outcomes.^28 30^

Readily available computer games using body motion for control, for example, the Nintendo Wii, have already been researched in clinical settings as treatment support tools.^33^ Though the issue with off-the-shelf games is that they are not designed as a medical device, hence lack proper validation for medical use. They may increase activity and motivation in a rehabilitation process, yet have been designed for entertainment purposes.^38^ Furthermore, these games usually require larger consoles that limit the patient in performing the exercises anywhere they want.

To the authors’ knowledge, this study is the first study focusing on a validated, wearable-controlled serious game designed to act as a medical support tool for wrist rehabilitation. This game and similar interventions may decrease the ever-growing burden wrist injuries pose to patients and to society, and can make validated wrist exercise therapy easily accessible for anyone. This study will contribute to the advancements of serious games for traumatic and non-traumatic wrist and other injuries, and may pave the way for future development and validation of wearable-controlled rehabilitation games.
